### Participating hospitals

This is a single centre study that will be conducted at the Complete Fertility Centre, a tertiary unit within the University Hospital Southampton NHS Foundation Trust.

### Randomisation

After collection of baseline data in the cycle prior to the intervention commencing, participating couples will be randomised to one or other of the study arms. The research team will be blinded to the randomisation. Stratification will be performed at randomisation for planned mode of fertilisation: in vitro fertilisation or intra-cytoplasmic sperm injection.

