### Primary and secondary endpoints

The primary endpoint is the mean period in hours for the cleaved embryos from participants in each arm of the study to develop from the 2 cell to the 3 cell stage (CC2). Secondary endpoints include using the Embryoscope to examine embryo quality, including S2 (synchrony during second set of cleavage divisions), T5 (time between fertilisation and the five cell embryo formation)
[14, 24], CC3 (duration of the third cell cycle)
[24], and the appearance and disappearance of the pronuclei
[25]. Nutritional markers, including the concentration of fatty acids, Vitamins D, B12, and B6, folate, prostaglandin E2 (PGE2) and prostaglandin F2α (PGF2α) will be measured in blood, endometrial fluid and follicular fluid pre and post intervention. Changes in endometrial tissue immune cell populations will also be examined. In male participants, changes in semen quality pre and post dietary intervention will be recorded according to standard parameters.

Implantation rates and pregnancy outcomes will be recorded and analysed. These include antenatal ultrasound markers; such as crown-rump length at 7 weeks and 12 weeks and fetal head and abdominal circumference, femur length and cross sectional metaphyseal area and placental volume at 20 weeks gestation. Perinatal measurements including birthweight and length and placenta dimensions and weight will also be recorded. Participants will be invited to bring their neonate to undergo a Dual energy X-ray Absorptiometry (DXA) to measure bone mineral content and density soon after birth.

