### Statistical analysis

#### Sample size and power considerations

In a previous retrospective study from our group, a diet rich in the omega-3 FAs was shown to be associated with improved embryo morphology when assessed on day 3 post fertilisation. Using a published scoring system between 1 (highest quality) and 5 (lowest quality), embryos generated in women with a daily mean total intake of omega-3 FAs in the 4 weeks prior to IVF greater than 1.7 g scored a mean of 0.6 (SE 0.26) points higher than those embryos derived from a woman reporting an intake of <1 g per day. Recently, morphokinetic analysis of human embryos has shown the duration of key development phases to be correlated to standard conventional morphological criteria, but more highly predictive of implantation potential
[14, 26]. One of the most sensitive predictors of implantation has been shown to be CC2. Embryos with a CC2 shorter than 11.9 hours (pooled SD 2.25 hours, but not normally distributed) have been reported to have an implantation rate of 35% compared to 28% when this key developmental step took longer than 11.9 hours. Moreover, in a study correlating morphokinetic parameters with static morphology scoring, a CC2 less than 11.9 hours was shown to correlate with an overall increase in embryo score of 0.5 points on a 5 point scale
[14]. This is similar in magnitude to the impact on embryo morphology reported to be achieved by exposure to a high omega 3 FA diet as described above
[4].

The primary end point of this study is therefore the difference in mean CC2 score of embryos generated by IVF after exposure of the couple to the intervention versus control diet. In order to detect a minimum absolute difference of 12% (1.4 hours) in mean CC2, or effect size of 0.670, with power ≥80% at p <0.05 a non-parametric comparison (Wilcoxon test) indicates a requirement of 46 couples per group in the analysis.

To allow for drop outs and failure to produce sufficient viable embryos, a further 20% will be recruited. This requires the randomisation of a minimum of 55 couples per group (110 in total).

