### Data analysis

In order to adjust for pre-defined confounders such as age, AMH level, ovarian stimulation method, fertilisation method and the number of oocytes obtained, univariate and multivariate analyses will be performed. This will enable the independent contribution of the dietary factor to the primary and secondary outcome measures to be quantified.

Differences in embryo quality parameters will be tested by Wilcoxon testing, and differences in blood and endometrial fluid levels of the stated secondary outcome parameters will be tested by the Mann Whitney U test.

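### Randomisation is stratified by planned IVF or ICSI, but the Wilcoxon test used for sizing and named for embryo parameters ignores the stratum, and the adjusted analysis is neither declared primary nor tied to planned mode

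*Protocol article*

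**What the plan says.** Four statements in the protocol article bear on this.

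- **Randomisation** names one stratification factor: "Stratification will be performed at randomisation for planned mode of fertilisation: in vitro fertilisation or intra-cytoplasmic sperm injection".
- **Sample size and power considerations** sets the target as a "minimum absolute difference of 12% (1.4 hours) in mean CC2, or effect size of 0.670" and derives 46 couples per group from a Wilcoxon comparison. No stratum enters the calculation.
- **Data analysis** names the test: "Differences in embryo quality parameters will be tested by Wilcoxon testing". Again no stratum is mentioned.
- **Data analysis** also plans an adjusted analysis and lists its covariates: "pre-defined confounders such as age, AMH level, ovarian stimulation method, fertilisation method and the number of oocytes obtained, univariate and multivariate analyses will be performed". The purpose follows: "This will enable the independent contribution of the dietary factor to the primary and secondary outcome measures to be quantified".

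So fertilisation method does appear in a planned analysis of the primary outcome. The article does not say whether that analysis or the Wilcoxon test decides the primary endpoint. It also does not say whether fertilisation method means the mode planned at randomisation or the mode eventually used.

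**The concern.** Stratified allocation balances the arms within planned IVF and within planned ICSI. If the two modes differ in embryo timing, that balance removes a source of chance difference between the arms. A test that ignores the strata still counts the between-mode spread as noise, so its reference distribution is too wide. Its true type I error falls below 5% and some power is lost. The test is not biased.

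The adjusted model does not clearly repair this. It is not named as primary, and its covariate is not tied to the stratum. Planned mode is fixed before the diet begins. Both partners take the diet and semen is analysed again just before insemination, so the mode used could be settled after the intervention. The article does not say how often the two differ. The same model also includes the number of oocytes obtained, which is known only after the diet, so it could not serve unchanged as a comparison adjusted for the stratum alone.

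**Working it through.** **Inputs from the protocol article.** Difference 1.4 h; SD 2.25 h ("pooled SD 2.25 hours, but not normally distributed"); printed effect size 0.670; 46 couples per group; power at least 80%; p < 0.05, taken as two-sided.

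**Assumptions.** The IVF-ICSI gap in CC2 and the IVF:ICSI split are not in the documents. I use gaps of 0 to 1.0 SD and a 50:50 split. Data are simulated as normal, although the article says CC2 is not.

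**Step 1: the plan's own figure.** Noether's formula for the two-sample Wilcoxon test is n per group = (z₀.₉₇₅ + z₀.₈₀)² / [6(P − 0.5)²], with P = Φ(d/√2).

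- d = 1.4/2.25 = 0.622: P = 0.670, so n = (1.960 + 0.842)² / [6 × 0.170²] = 45.3, rounded up to 46. The stated figure is reproduced.
- d = 0.670: P = 0.682, so n = 39.4, rounded up to 40.

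The 46 thus comes from a two-group test with no stratum, and at 0.622 power is only a little above 80%.

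**Step 2: effect of stratifying.** Simulation with 20,000 trials per setting, 46 per arm, arms balanced within two equal strata, and total SD fixed at 1. With gap g (in total SDs), the strata explain g²/4 of the variance and the within-stratum SD is √(1 − g²/4). Effect 0.622:

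| Gap (SD) | Unstratified power | Stratified (van Elteren) power | Change (points) | Unstratified type I error | Stratified type I error |
|---|---|---|---|---|---|
| 0 | 82.4% | 81.8% | −0.6 | 4.7% | 4.6% |
| 0.25 | 82.2% | 81.9% | −0.3 | 4.8% | 4.9% |
| 0.5 | 83.2% | 84.4% | +1.2 | 4.6% | 5.2% |
| 0.75 | 83.6% | 86.6% | +3.0 | 3.5% | 4.8% |
| 1.0 | 84.7% | 90.8% | +6.1 | 2.4% | 4.8% |

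Repeat simulations put the cost at no gap between 0.6 and 0.8 points, the gain at 1.0 SD between 5.7 and 6.2 points, and the unstratified type I error there between 2.1% and 2.5%. At effect 0.670 the pattern is the same: 87.4% to 86.9% with no gap, 88.1% to 89.0% at 0.5 SD, 89.8% to 94.3% at 1.0 SD.

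**Step 3: check on the type I error.** Under the null, the unstratified statistic has SD of about √(1 − g²/4), so its true size is about 2[1 − Φ(1.96/√(1 − g²/4))]. At g = 1.0 this is 2[1 − Φ(1.96/0.866)] = 2.4%. At g = 0.75 it is 2[1 − Φ(1.96/0.927)] = 3.4%. Both agree with the simulation.

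**The case against.** The strongest reply has four parts.

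1. *The stratifier is not ignored.* Data analysis adjusts the primary and secondary outcomes for fertilisation method, and regression on mode is one of the remedies proposed here. This stands in part. A reader might infer that no planned analysis uses mode of fertilisation, or that the covariate is the mode actually used. The article supports neither: it leaves planned versus actual open. What remains is that the analysis is not declared primary and the covariate is not linked to the stratum.

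2. *A stratified Wilcoxon test is still a Wilcoxon test, and a condensed article may leave that detail to a fuller document.* That is possible. But the article names both the stratifier and the test, and its sample size is that of the two-group test, so this is a stated choice that can be improved and not just a missing detail.

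3. *No mechanism is shown for the primary endpoint.* This largely stands. CC2 runs from the 2-cell to the 3-cell stage, so it may be less exposed to insemination mode than T5, which is timed from fertilisation, or the pronuclear timings. Those are secondary.

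4. *A large gain needs a large gap.* This stands. On the article's SD, 1.0 SD is 2.25 h, which is 2.25/1.4 = 1.6 times the whole target difference. A reader might also infer that power could drop to about 70%. That arises only if a 1.0 SD gap is added on top of a fixed within-stratum SD, which raises total SD by a factor of √1.25 = 1.12 above the planning value, and if the effect is set at 0.6. With total SD held at the planning value, unstratified power stays at 82% or more in every setting above.

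**Conclusion.** The point holds as a conditional loss of precision. It is not an error that invalidates the test or leaves the trial below its planned power. The test used for sizing and named for embryo parameters takes no account of the single stratification factor, and nothing in the article ties the adjusted analysis to that factor or makes it primary.

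Stratifying costs under one point of power if mode is not prognostic, gains about one point at a 0.5 SD gap, about three at 0.75 SD and about six at 1.0 SD. These figures rest on normal data, an even split, exact balance within strata and a gap that the documents do not supply. Choosing mode as the only stratifier, and listing fertilisation method among the confounders, suggests that the investigators regard it as prognostic, but this says nothing about the size of the gap.

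**What to change.** Make the primary test a couple-level stratified Wilcoxon (van Elteren) test of mean CC2 by planned mode of fertilisation, or a couple-level regression with planned mode as covariate. State which of the two decides the primary endpoint. Use the same approach for all embryo-timing endpoints: CC2, CC3, S2, T5 and the pronuclear timings. In the adjusted model, define fertilisation method as the planned mode recorded at randomisation.

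The cost is a line or two of analysis wording. The stratum must already be recorded in order to randomise, so no new data are needed and the sample size need not change. The only downside is the power loss of under one point if mode has no bearing on timing.

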### Data collection

Data collection will be performed using a case report form (CRF). Data relating to clinical treatment outcomes, including embryo quality measurements will be acquired from the Fertility Unit’s electronic data collection system. Questionnaire responses will be inputted electronically into the CRF. Additional data relating to laboratory assays will be obtained directly from the laboratory’s database or the respective external laboratories and entered into the CRF. This minimises the risk of transcription errors; however, all data will be verified and cleansed prior to analysis.

### Statistical analysis

#### Sample size and power considerations

In a previous retrospective study from our group, a diet rich in the omega-3 FAs was shown to be associated with improved embryo morphology when assessed on day 3 post fertilisation. Using a published scoring system between 1 (highest quality) and 5 (lowest quality), embryos generated in women with a daily mean total intake of omega-3 FAs in the 4 weeks prior to IVF greater than 1.7 g scored a mean of 0.6 (SE 0.26) points higher than those embryos derived from a woman reporting an intake of <1 g per day. Recently, morphokinetic analysis of human embryos has shown the duration of key development phases to be correlated to standard conventional morphological criteria, but more highly predictive of implantation potential
[14, 26]. One of the most sensitive predictors of implantation has been shown to be CC2. Embryos with a CC2 shorter than 11.9 hours (pooled SD 2.25 hours, but not normally distributed) have been reported to have an implantation rate of 35% compared to 28% when this key developmental step took longer than 11.9 hours. Moreover, in a study correlating morphokinetic parameters with static morphology scoring, a CC2 less than 11.9 hours was shown to correlate with an overall increase in embryo score of 0.5 points on a 5 point scale
[14]. This is similar in magnitude to the impact on embryo morphology reported to be achieved by exposure to a high omega 3 FA diet as described above
[4].

The primary end point of this study is therefore the difference in mean CC2 score of embryos generated by IVF after exposure of the couple to the intervention versus control diet. In order to detect a minimum absolute difference of 12% (1.4 hours) in mean CC2, or effect size of 0.670, with power ≥80% at p <0.05 a non-parametric comparison (Wilcoxon test) indicates a requirement of 46 couples per group in the analysis.

To allow for drop outs and failure to produce sufficient viable embryos, a further 20% will be recruited. This requires the randomisation of a minimum of 55 couples per group (110 in total).

### Data analysis

In order to adjust for pre-defined confounders such as age, AMH level, ovarian stimulation method, fertilisation method and the number of oocytes obtained, univariate and multivariate analyses will be performed. This will enable the independent contribution of the dietary factor to the primary and secondary outcome measures to be quantified.

Differences in embryo quality parameters will be tested by Wilcoxon testing, and differences in blood and endometrial fluid levels of the stated secondary outcome parameters will be tested by the Mann Whitney U test.

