**Flowchart of eligible patients.**

### Study design

The PREPARE trial is a single centre, randomised controlled trial, powered to demonstrate a difference in mean duration of the second cell cycle (CC2) of embryos generated by IVF after exposure of the couple to the intervention versus control. Both the male and female in the intervention group will receive a six week diet of olive oil for cooking, an olive oil based spread, and a daily supplement drink enriched with Vitamin D (10 micrograms) and the marine omega-3 FAs EPA (1 g) and DHA (1 g daily) versus the control diet of sunflower seed oil for cooking, a sunflower oil based spread, and a daily supplement drink without vitamin D, EPA or DHA.

Following inclusion into the study but prior to randomisation, consenting participants will be invited to complete a preconception questionnaire and the short Southampton Food Frequency Questionnaire (FFQ) in order to characterise their lifestyle and diet prior to entry into the study
[21]. At this time, samples of blood, uterine fluid and endometrium will be obtained from the women in order to provide baseline data of the nutritional and immune cell content prior to the intervention. The male participants will be asked to provide a semen sample which will be analysed for concentration, motility and morphology according to the WHO criteria
[22].

The women embarking on the study will undergo ovarian stimulation according to our standard protocol, provided no abnormality is seen on their baseline scan on day 2 of their cycle. Oocyte retrieval will be performed 36 hours following the single dose of human chorionic gonadotrophin (hCG), which promotes oocyte maturation. At the point of oocyte retrieval, further blood will be taken from the female participants and the follicular fluid and cumulus cells that are routinely removed, during IVF-ICSI, from the oocyte prior to insemination will be snap frozen. A further semen sample from the males will be analysed according to the WHO criteria prior to insemination.

The embryos will be cultured in Vitrolife IVF media in a validated time lapse incubator (Embryoscope, Unisense, FertiliTech, Denmark) in 5% CO2, 5%O2 and at 37°C. During the incubation, twenty one plane focal images will be generated every hour and analysed according to morphological and morphokinetic markers

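### The model meant to quantify the diet effect adjusts for number of oocytes obtained, a post-randomisation variable that cannot be a confounder and may be a mediator or collider

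*Protocol article*

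**What the plan says.** The Data analysis section plans univariate and multivariate analyses to adjust for "pre-defined confounders such as age, AMH level, ovarian stimulation method, fertilisation method and the number of oocytes obtained". It gives the purpose as follows: "This will enable the independent contribution of the dietary factor to the primary and secondary outcome measures to be quantified". The same section says that embryo quality parameters will be compared by Wilcoxon testing.

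The order of events is in two other sections:

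- **Randomisation:** "After collection of baseline data in the cycle prior to the intervention commencing, participating couples will be randomised". The same section adds: "Stratification will be performed at randomisation for planned mode of fertilisation".
- **Study design:** the women "will undergo ovarian stimulation according to our standard protocol", and oocytes are retrieved 36 hours after hCG. On the male side, "A further semen sample from the males will be analysed according to the WHO criteria prior to insemination".

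**The concern.** In a randomised comparison, confounders are common causes of allocation and outcome, and randomisation removes them by design. A variable that arises after allocation cannot be one. It can only be a consequence of treatment, a marker of other causes of the outcome, or both.

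Number of oocytes obtained is such a variable, yet the protocol lists it with age and AMH as if it were of the same kind. Two things can go wrong if diet affects oocyte yield:

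- **Mediation.** If yield in turn affects the outcome, holding it fixed removes that part of the diet effect.
- **Collider bias.** If an unmeasured cause, such as ovarian quality, drives both yield and embryo timing, conditioning on yield links diet to that cause.

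In either case the coefficient for diet is no longer the total effect of being assigned to the diet. A reader would nevertheless take it as that, because the protocol gives this model the task of quantifying the dietary contribution.

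**Working it through.** **1. Timing of each named covariate**

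| Covariate | What the article shows | Status |
|---|---|---|
| Age, AMH | Eligibility characteristics (Study population and recruitment) | Baseline |
| Fertilisation method | Data analysis says neither planned nor used; the planned mode is the stratification factor (Randomisation) | Baseline if planned mode is meant |
| Ovarian stimulation method | Standard protocol; no statement of when the method is chosen (Study design) | Not determinable |
| Number of oocytes obtained | Counted at retrieval, after stimulation and hCG (Study design), hence after randomisation and after the diet has started | Post-randomisation |

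Only the last row is post-randomisation on every reading.

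**2. The scale, checked against the protocol's own figure**

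The sample size section gives a difference of 1.4 h, an SD of 2.25 h, an effect size of 0.670 and 46 couples per group for a Wilcoxon test at 80% power. I take the 5% level as two-sided; the article does not say.

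- Standardised difference: d = 1.4 / 2.25 = 0.622.
- Probability form used by Noether's formula: p = Φ(d/√2) = Φ(0.440) = 0.670. This equals the printed effect size.
- n per group = ½ × (1.960 + 0.842)² / [3 × (p − 0.5)²] = ½ × 7.85 / (3 × 0.170²) = 45.3, rounded up to 46.

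The protocol's figure is reproduced, so 2.25 h is the SD on which the trial was sized. The present point does not change the 46.

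**3. Size of the possible bias**

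Let δ be the shift in oocyte number caused by diet, in SD units, and r the standardised within-arm slope of CC2 on oocyte number. In a linear model the adjusted effect differs from the total effect by δ × r × SD in absolute value. The documents give neither δ nor r, so both are assumed.

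| δ | r | Bias (h) | Share of 1.4 h |
|---|---|---|---|
| 0 | any | 0 | 0% |
| any | 0 | 0 | 0% |
| 0.2 | 0.1 | 0.2 × 0.1 × 2.25 = 0.045 | 3% |
| 0.3 | 0.3 | 0.3 × 0.3 × 2.25 = 0.20 | 14% |
| 0.5 | 0.3 | 0.5 × 0.3 × 2.25 = 0.34 | 24% |

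The sign can go either way, depending on the signs of δ and r.

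**4. Simulation check (all parameters assumed)**

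The true total effect on CC2 was set at −1.4 h. Oocyte number was in SD units and entered linearly. In some settings an unmeasured cause was shared by oocyte number and CC2.

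- Diet does not shift oocyte number: adjusted effect about −1.4 h, no bias.
- Shift of 0.2 SD: adjusted effect from −1.40 to −1.19 h.
- Shift of 0.5 SD: adjusted effect from −1.40 to −0.89 h.
- Unadjusted effect: about −1.4 h throughout.

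The far end exceeds the table because its within-arm slope, 0.5 + 0.7 × √0.5 = 0.995 h per SD, is about 0.43 in standardised terms (0.995 / 2.29, the within-arm SD in that setting). That is steeper than the 0.3 assumed above. Where CC2 was unrelated to oocyte number and its causes, a diet shift alone gave no bias.

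**The case against.** The strongest reply is that the powered comparison is untouched. The trial is sized on a Wilcoxon test of CC2, the Data analysis section plans Wilcoxon testing of embryo quality, and that test uses no covariates. This stands. A reader might infer that the primary test itself is biased; it is not. What remains exposed is the effect estimate, since the article assigns quantification of the diet effect to the adjusted model and does not formally rank the two analyses.

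Second, a reader might infer that all three treatment-cycle covariates are wrong. The article does not support this.

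- **Fertilisation method.** It can be read as the planned mode used for stratification, and adjusting for that is correct. The retrieval-day semen sample precedes insemination, and "changes in semen quality pre and post dietary intervention will be recorded" as a secondary endpoint, so a diet-dependent change of method is conceivable. But nothing says that the method is changed on that sample, or that the method used enters the model. This is an ambiguity to settle, not an error.
- **Stimulation method.** It is delivered after randomisation, but the article does not say when it is chosen or suggest that diet could alter the choice.

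Third, it is tempting to say that the adjusted estimate *is* biased. Nothing in the article says that diet is expected to change oocyte *number*. The Discussion speaks of the nutritional and immune environment of the oocyte, and names oocyte number after gonadotrophin stimulation as a factor in pregnancy rate alongside diet. So the bias is conditional and may be zero. The same remark does link oocyte number to pregnancy, though. For pregnancy outcomes, if they are analysed with this model, only the link from diet to yield is left open.

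Fourth, the SD of 2.25 h is reported in a sentence about embryos. If couple means vary less, the figures in hours fall in proportion.

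Finally, the open wording of the covariate list could look like a fault too. A closed list is commonly left to the analysis plan, which is not shown, so I do not count it.

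**Conclusion.** The point holds for number of oocytes obtained. It is measured after randomisation and after the diet has begun, so calling it a confounder is wrong on any reading. A model that conditions on it does not estimate the total effect of assignment if diet changes yield and if yield, or a shared cause, relates to the outcome.

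How far this matters is unknown. On the primary endpoint the range is 0 to about 0.34 h, or 0 to 24% of the 1.4 h target. That rests on an assumed shift of 0 to 0.5 SD, an assumed standardised slope of 0 to 0.3 and the protocol's SD of 2.25 h; a steeper slope would widen it. Neither the sample size nor the error rate of the unadjusted Wilcoxon test is affected. For fertilisation and stimulation method, the documents support a request for clarification and no more.

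**What to change.** - Remove number of oocytes obtained from the model that estimates the diet effect.
- Report oocyte number by arm as an outcome, and label any model that contains it exploratory.
- State that fertilisation method enters as the planned mode used for stratification.
- Keep stimulation method only as the method fixed before randomisation.

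This changes analysis wording only: no extra data, visits or couples. The one real cost is the possible loss of some precision that oocyte number might have brought. The change should be made before any unblinded analysis, because dropping a covariate afterwards could look driven by the data.

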[23]. For women in whom embryo transfer is possible, uterine fluid aspiration will be carried out prior to the procedure. In those not undergoing embryo transfers, an endometrial biopsy will also be performed.

Compliance with the diet will be monitored by a daily diary completed at home by the couple and by counting the empty cartons when they are returned to the Fertility Unit (Figure 
2).

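### Blood and endometrial-fluid markers are assigned an unadjusted Mann-Whitney test although their baselines are collected, and follicular fluid is promised before and after the diet with no sample taken before it

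*Protocol article*

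**What the plan says.** All references are to the protocol article.

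- **Baseline sampling (Study design).** Before randomisation, "samples of blood, uterine fluid and endometrium will be obtained from the women in order to provide baseline data". The Randomisation section places this step: "After collection of baseline data in the cycle prior to the intervention commencing". Follicular fluid is not among the baseline samples.
- **Later sampling (Study design).** Blood is taken again at oocyte retrieval. Follicular fluid appears only at that visit: "the follicular fluid and cumulus cells that are routinely removed, during IVF-ICSI, from the oocyte prior to insemination will be snap frozen". For endometrial fluid, "For women in whom embryo transfer is possible, uterine fluid aspiration will be carried out prior to the procedure".
- **Endpoints (Primary and secondary endpoints).** The nutritional markers "will be measured in blood, endometrial fluid and follicular fluid pre and post intervention".
- **Tests (Data analysis).** For the markers, "differences in blood and endometrial fluid levels of the stated secondary outcome parameters will be tested by the Mann Whitney U test". No test is named for follicular fluid. The same section announces univariate and multivariate analyses adjusting for "pre-defined confounders such as age, AMH level, ovarian stimulation method, fertilisation method and the number of oocytes obtained", so as to allow "the independent contribution of the dietary factor to the primary and secondary outcome measures to be quantified".

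**The concern.** There are two separate matters.

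**Use of baseline.** The trial goes to the trouble of taking blood and uterine fluid before the diet, then assigns the markers a two-sample rank test that takes no covariate. Whether the test is applied to post-intervention values or to changes is left open, and the two choices have different power. The nutritional content of the intrauterine environment is the secondary outcome named in the Abstract, and the number of couples was set for CC2, not for the markers. Efficiency in the marker analyses is therefore worth having.

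**Follicular fluid.** The endpoints section lists it with the fluids measured at both time points, but the sampling schedule provides only the later one. An analysis plan cannot supply a measurement for which no sample is taken.

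**Working it through.** **1. The plan's own figure.** The article states no power for the markers. Its only sample size is 46 couples per group for CC2, from a difference of 1.4 h and an SD of 2.25 h. Noether's formula for the Wilcoxon test, two-sided 5% (sidedness assumed) and 80% power:

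- d = 1.4/2.25 = 0.622, so p = Φ(0.622/√2) = 0.670, which matches the article's stated effect size if that is read as this probability.
- Total N = (1.960 + 0.842)² / [3(p − 0.5)²] = 90.5, hence 46 per group.

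The 46 reproduces. It is used below only as a convenient group size.

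**2. Variance under three analyses.** Let ρ be the correlation between a marker's baseline and post-intervention value, with equal variances. Relative to the variance of the post value:

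- post levels: 1
- change from baseline: 2(1 − ρ)
- ANCOVA on baseline: 1 − ρ²

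For ρ between 0 and 1, 1 − ρ² ≤ 1 and 2(1 − ρ) − (1 − ρ²) = (1 − ρ)² ≥ 0. ANCOVA therefore has no larger variance than either reading of the Mann-Whitney sentence, whatever ρ is.

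**3. Power by simulation.** Assumptions: normal data, 46 per arm, a true difference of 0.5 SD, two-sided 5%, 3,000 runs. Simulation error is about √(0.63 × 0.37/3000) = 0.9 percentage points. Neither ρ nor the 0.5 SD comes from the article.

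| ρ | Mann-Whitney, post levels | Mann-Whitney, change | ANCOVA | Rank ANCOVA |
|---|---|---|---|---|
| 0 | 63% | 36% | 65% | 63% |
| 0.3 | 65% | 50% | 70% | 68% |
| 0.5 | 63% | 65% | 78% | 76% |
| 0.7 | 63% | 85% | 91% | 87% |

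**4. Detectable difference at 80% power.** For means, (1.960 + 0.842) × √(2/46) = 0.584 SD.

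- Mann-Whitney on post levels (relative efficiency 0.955): 0.584/√0.955 = 0.60 SD.
- ANCOVA, 0.584 × √(1 − ρ²): 0.56, 0.51 and 0.42 SD at ρ = 0.3, 0.5 and 0.7.
- Equivalent group size for an unadjusted comparison of post-value means, 46/(1 − ρ²): about 51, 61 and 90.

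**5. Follicular fluid, text against text.**

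| Fluid | Before the diet | After the diet |
|---|---|---|
| Blood | yes | yes, at retrieval |
| Endometrial (uterine) fluid | yes | yes, before transfer where transfer is possible |
| Follicular fluid | none | yes, at retrieval |

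The first two rows agree with the endpoint statement. The third does not.

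**The case against.** The strongest reply is that the article does not rule out baseline adjustment. Multivariate analyses are promised for secondary outcomes as well as the primary, the covariates are offered as examples, and the full covariate set may stand in an analysis plan that is not shown. This is right as far as it goes: a reader might infer that the trial throws its baseline data away, and the text does not show that. What remains is that the article does name a test for these markers, that this test takes no baseline covariate, and that its input is left undefined.

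It is also right that the matter is one of efficiency. A reader might infer that the Mann-Whitney test is biased by chance imbalance at baseline. It is not: on post-intervention values it is a valid randomised comparison whose error rate already allows for such imbalance.

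The power figures are open to challenge too. Correlation and effect are assumed. Baseline comes from the cycle before the diet and the later sample from a stimulated cycle, so the correlation may be low, above all in endometrial fluid. Post-intervention endometrial fluid is explicitly described only for women in whom transfer is possible, so fewer than 46 per arm may contribute. All of this stands. It limits the size of the gain, but not the ordering of the methods.

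Two further inferences lack support. The Mann-Whitney sentence covers blood and endometrial fluid only; no test is named for semen, and the endpoints section says that changes in semen quality will be recorded. And although the endpoints are described before and after the diet, no within-arm test is planned; Mann-Whitney compares two independent groups.

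On follicular fluid, the reply is that the sampling schedule makes the true position clear and no named test depends on it. That makes the repair easy, but the two sections still disagree.

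**Conclusion.** The point holds in a limited form.

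- **Markers in blood and endometrial fluid.** The named analysis is valid but under-specified, and less efficient than one adjusted for the marker's own baseline. At 46 per arm and an assumed 0.5 SD difference, adjustment moves power from about 63–65% to about 70%, 78% or 91% at correlations of 0.3, 0.5 or 0.7. At zero correlation there is nothing to gain and essentially nothing to lose. These are illustrations under normality, not estimates for this trial.
- **Follicular fluid.** The contradiction is plain and needs no assumption: a measurement before the diet is promised and no sample is scheduled for it.

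The primary comparison of CC2 is not affected by either part.

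**What to change.** 1. In Data analysis, make the main analysis of each blood and endometrial-fluid marker a between-arm ANCOVA: post-intervention value (log or rank scale if skewed) on arm, the marker's own baseline, and planned mode of fertilisation, which is the stratification factor.
2. If Mann-Whitney is kept as a supporting analysis, say whether it uses post-intervention values or changes.
3. Reconcile Primary and secondary endpoints with Study design by defining the follicular-fluid markers as a post-intervention comparison between arms, and name the test for them.

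The cost is a few sentences. The baseline samples are already planned, and no visit, sample or participant is added.
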